To address these challenges, we designed a randomized controlled trial (RCT) with a 3-month crossover design, where SCS, DRGS or SCS+DRGS (DUAL) will be proposed to a single patient presenting with refractory chronic lower limb neuropathic pain (e.g., CRPS, diabetic foot peripheral neuropathy, foot and ankle peripheral neuropathy, radicular pain associated with PSPS-T2) and/or documented neuropathic refractory back pain. After the crossover period, all patients will be switched to burst waveform with 1-month follow-up, and at 4-month follow-up, they will be asked to choose SCS, DRGS or SCS+DRGS with tonic conventional or burst waveform.

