### 2.1. Design and Setting

The BOOST DRG study is divided into two phases.

Phase A (Pilot study) is a randomized, double-blinded, crossover, six-arm study evaluating the feasibility and comparing the efficacy of three stimulation modalities: SCS, DRGS and DUAL (SCS+DRGS) on 12 patients during 3-month follow-up, which will be conducted only in Poitiers University Hospital (France). According to the phase A results, in terms of feasibility and safety, a second phase is planned, following the same design and including a larger sample of patients, internationally, to take into account the variability of practices.

Phase B (Main study) is a prospective, multicentric, randomized, double-blinded, crossover, six-arm study comparing the efficacy of three stimulation modalities: SCS, DRGS and DUAL stimulation (SCS+DRGS) on 54 patients, conducted in the Poitiers University Hospital (France), the Colmar Louis Pasteur Hospital (France) and in Genève Tower Hospital Pain Clinic/Lausanne University Hospital (Switzerland).

Phase A and phase B have the same design. Patients will be implanted with the Octrode^TM^ contact percutaneous lead for SCS and one or several Quattrode^TM^ lead(s) for the DRGS, enabling use of the three different stimulation modalities in the same patient. The leads will be connected to a single external pulse generator. Patients will be randomized in 6 different arms in a 1:1:1:1:1:1 ratio: SCS alone, DRGS alone and DUAL stimulation. During the 3-month crossover period, patients will be under the tonic conventional stimulation (TCS) waveform, whatever the stimulation modality. Each stimulation modality will be administered for 1 month. Patients will be assessed at the end of each stimulation modality period, corresponding to the 1-month, 2-month and 3-month follow-up visits. At the end of the crossover period, stimulation modality will not be changed and will be switched to the burst waveform for 1 month. Patients will be assessed at the end of this 1-month period, corresponding to the study’s 4-month follow-up visit. Patients will then decide which stimulation modality and waveform they prefer and will be assessed at 6 months and 12 months.

Patient flow and the study design are presented in Table 1 and Figure 1, respectively.

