### 2.6. Procedures to Minimize Bias

To minimize selection bias, the randomization list will be prepared using the random selection program Ennov Clinical. Randomization numbers will be assigned in strict sequence; when a subject is confirmed as eligible for randomization, the next unassigned randomization number in sequence will be given. Randomization allocation will be concealed from the evaluator and subject, using a centralized automatic web-based data management system dedicated to the study and accessible to investigators by username and personal password (CS Online 7.5.10.11). Once assigned, the randomization assignment for the subject cannot be changed. Early departure from the study does not give rise to placement or reassignment of the rank of inclusion.

Due to the paresthesia generated by the TCS waveform, during the crossover period, patients will be under TCS waveform, whatever the type of stimulation. Consequently, patients will not be able to distinguish if they are under DRGS, SCS or DUAL stimulation. At the 3-month follow-up visit, all the patients will be switched to the burst waveform for a 1-month period while keeping the last allocated stimulation type in the randomized crossover arm. Patients will keep their stimulation in order to achieve optimal comparability between TCS and burst parameters.

To allow for investigator blinding, the evaluator will be different from the person who programs the IPG.

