#### 2.7.2. Main Statistical Analysis

Statistical analysis will be conducted using R software (Version 3.1.2, R Foundation for Statistical Computing, Vienna, Austria).

Data from phase A (12 patients) and phase B (54 patients) will be pooled (66 patients) for the main analysis.

Normality of distributions will be tested using the Shapiro–Wilk test. Either parametric or non-parametric methods will be used depending on the normality test results.

Our primary objective is to compare the efficacy of SCS, DRGS and DUAL stimulation at the crossover period based on the “50% VAS decrease” outcome.

Since our primary endpoint is a binary variable, we will use a mixed-effects logistic regression model, where the fixed effects are as follows: the treatment effect, the period effect and their interaction. The random effect is the random subject intercept. Fixed effects, their 95% confidence intervals and their significant level will be reported. Models will be estimated using restricted maximum likelihood estimation using the lmer function from the lmerTest package.

In case of significant effect of period and treatment, a two-step procedure will be conducted to assess pairwise differences between treatment effects. First, treatment effects will be estimated using a mixed-effects model as previously described, using data from each pair of treatments. Next, we will apply Holm–Bonferroni method to keep family-wise error under the 0.05 significance level.

In case the period effect is not significant, a Cochran Q test will be used to test the differences between the three groups. If the null hypothesis of the Cochran Q test is rejected, a McNemar test will be conducted for pairwise comparisons of the three groups. A Holm–Bonferroni correction will be applied to the *p*-values following the pairwise comparisons.

For the secondary outcomes, a two-factor repeated measure ANOVA (treatment + period factors) will be used to compare the continuous outcomes between the three treatments and a mixed effect logistic/multinomial regression model will be used to compare the categorical outcomes similarly to the analysis of the primary outcome. If the omnibus test’s *p*-value is significant, a pairwise comparison procedure with Holm–Bonferroni correction will be conducted.

At the 4-month period, the proportions of patients preferring the DRGS, the conventional SCS or the DUAL stimulation will be compared using a Chi-squared test.

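### The only target-preference test uses the month-4 choice, made after an extra burst month on the last target alone, so it mixes target preference with recency and burst experience

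*Protocol article*

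**What the plan says.** All references are to the protocol article.

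- **Crossover.** Section 2.1: "Each stimulation modality will be administered for 1 month", all under tonic stimulation, ending at the 3-month visit.
- **Allocation.** Section 2.1: "Patients will be randomized in 6 different arms in a 1:1:1:1:1:1 ratio". Six arms with three treatments is read here as the six possible orders.
- **Burst month.** Section 2.1 says that after the crossover the "stimulation modality will not be changed and will be switched to the burst waveform for 1 month". Section 2.6 adds that this is done "while keeping the last allocated stimulation type in the randomized crossover arm", and gives comparability of tonic and burst as the reason.
- **Choice.** The Introduction says that "at 4-month follow-up, they will be asked to choose SCS, DRGS or SCS+DRGS with tonic conventional or burst waveform". Section 2.1 gives the same order of events: "Patients will then decide which stimulation modality and waveform they prefer and will be assessed at 6 months and 12 months".
- **Test.** Section 2.7.2: "At the 4-month period, the proportions of patients preferring the DRGS, the conventional SCS or the DUAL stimulation will be compared using a Chi-squared test". The sentence mentions neither the last target nor the chosen waveform.
- **Later use.** Section 2.7.2 also groups patients by preferred target and preferred stimulation type in a two-factor ANOVA at 6 and 12 months.

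**The concern.** At month 4 the three targets are not on an equal footing. One has been worn for two months, most recently, and under both waveforms. The other two have had one month each, tonic only. Patients choose among six target-by-waveform options but have tried four.

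A patient who likes burst can pick a burst option already experienced only by staying on the last target. A patient who dislikes burst met it only on that target. The test then adds the choices up over waveform and compares three target totals.

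Two consequences are possible. Patients who stay where they are pull the totals towards the randomised last target and hide a real preference. And if burst suits one target better than another, the totals can differ even when patients would be evenly split among the targets under tonic stimulation. The article itself raises the second possibility: section 3.4 warns that overstimulating the DRG is felt as pain and that permanent burst there may not be tolerable.

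**Working it through.** The article states no size or power for the preference test, so there is no figure to reproduce. The check asks how far the month-4 design could move the result.

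**Inputs from the article.** N = 66 (section 2.7.1); two-sided 5% level (section 2.7.2); 17% dropout, leaving 66 × 0.83 ≈ 54 to 55; each target last in one third of patients, 66/3 = 22.

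**Assumptions.** The test is a one-sample chi-squared test of three counts against equal shares. A fraction s_k of patients whose last target is k choose k because of recency or burst. Everyone else chooses by true preference π_k. No value of s_k or π_k is in the article.

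**Formula.** With each target last in one third of patients and s̄ the mean of the three s_k:

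expected share of k = (1 − s̄) × π_k + s_k/3

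Noncentrality for the formula-based power: λ = N × 3 × Σ(share − 1/3)², 2 degrees of freedom. Simulation with 22 patients per last target was run alongside, because fixed allocation narrows the spread of the counts and the formula ignores that.

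**1. No true preference, equal staying.** The shares remain 1/3 each. Simulated rejection at N = 66 is 4.3% and 2.7% with 20% and 40% staying, and about 4% and 2% with 25% and 50%. Recency alone creates no false preference.

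**2. True shares 50/30/20%, equal staying, N = 66.**

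| Staying | Expected shares | Power, formula | Power, simulated |
|---|---|---|---|
| 0% | 50/30/20% | 78% | 77% |
| 25% | 0.75 × π + 0.25/3 = 46/31/23% | 52% | 50% |
| 50% | 0.50 × π + 0.50/3 = 42/32/27% | 26% | 19% |

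For the first row, λ = 66 × 3 × (0.0278 + 0.0011 + 0.0178) = 9.24. Staying multiplies λ by (1 − s)², giving 5.20 and 2.31. At N = 54 simulated power is 68% with no staying, 47% with 20% staying and 25% with 40% staying.

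**3. No true tonic preference, staying differs by target, N = 66.** The first figure is the target that burst suits better or worse.

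| Staying | Share of that target | Simulated rejection |
|---|---|---|
| 40/20/20% | 0.733/3 + 0.40/3 = 37.8% | 8% |
| 30/10/10% | 0.833/3 + 0.30/3 = 37.8% | 9% |
| 50/25/25% | 0.667/3 + 0.50/3 = 38.9% | 10% |
| 25/0/0% | 0.917/3 + 0.25/3 = 38.9% | 12% |
| 0/30/30% | 0.800/3 + 0 = 26.7% | 14% (formula 16%) |
| 50/10/10% | 0.767/3 + 0.50/3 = 42.2% | 23.5% |
| 50/0/0% | 0.833/3 + 0.50/3 = 44.4% | 37% (30% at N = 54) |

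**The case against.** The strongest reply is that the month-4 choice is deliberate. It assigns treatment up to month 12, section 3.5 presents it as a benefit to the patient, and section 2.6 explains why the last target is kept. A patient who settles on SCS because burst works well there has a real preference for the option on offer. This stands: the choice is a legitimate pragmatic outcome. The fault lies only in reading its target totals as a comparison of targets alone.

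Further points that stand:

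- Preference is not the primary outcome (section 2.5.1), and it is not named among the secondary objectives or in the secondary outcome list of section 2.5.2. It rests on one sentence of section 2.7.2.
- PGIC is scheduled at M1, M2 and M3 (Table 1), so satisfaction after equal tonic exposure is already compared. It is a rating rather than a choice among the three, so it covers part of the gap.
- Section 3.4 speaks of permanent burst on the DRG, while section 2.4 specifies intermittent dosing. That weakens the expected difference between targets without removing it.

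A reader might also infer that no preference is recorded at M3. The article does not establish that: Table 1 has no preference row at any visit, including M4, and the full protocol is not shown. What is documented is that the stated test uses month 4. Nor does the Introduction's contrast between human evidence for burst SCS and animal evidence for burst DRGS show unequal tolerability; it concerns evidence of efficacy.

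**Conclusion.** The concern holds as a limit on interpretation and a cheap improvement. As planned, the month-4 test cannot separate target preference from recency and from burst experienced on a single target.

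The better-supported effect is dilution, which needs only that some patients stay where they are: power of about 77% becomes about 50% or 19% if 25% or 50% stay, for assumed true shares of 50/30/20% and N = 66. A reader might go further and expect the design to manufacture a target preference. The documents do not support that in general. Balanced orders prevent it when staying is equal across targets, and it requires burst to suit targets unequally, which section 3.4 makes plausible but does not quantify. Moderate assumed differences give roughly 8% to 16% rejection, and a 40-point contrast about 23%. The 37% figure needs half of one group and none of the other two to stay.

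All of these sizes rest on assumed rates. The tonic crossover primary endpoint is untouched.

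**What to change.** - **M3 visit.** Before the switch to burst, ask which crossover period (1, 2 or 3) the patient preferred, with the patient and evaluator still blinded. Map the answer to the target from the allocation list and use it for the formal chi-squared test in section 2.7.2.
- **M4 choice.** Keep it exactly as planned for follow-up to M6 and M12. Report it as target by waveform, tabulated by last crossover target (or analysed stratified by last target), and state that each patient experienced burst on one target only. Carry the same statement into the 6- and 12-month ANOVA grouped by preference.

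The cost is one question at an existing visit, one table and a wording change; no treatment, visit or sample size changes. The formal test would then cover tonic stimulation only. Period 3 would still be the most recent at M3, so some recency remains, but exposure time and waveform would be equal across targets and the order is balanced by the six arms.

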#### 2.5.2. Secondary Outcomes

Secondary outcomes that will be compared between treatments and waveforms are changed between baseline and each follow-up visit in each of the following scores: pain intensity (VAS), pain surface (in cm^2^), percentage of pain covered with paresthesia and lead selectivity (percentage of paresthesia covering pain); paresthesia discomfort measured by an 11-point numeric rating scale (NRS) while sitting, standing and lying down; health-related quality of life measured by the EuroQol 5 Dimensions 5 Level (EQ-5D-5L) questionnaire; functional disability measured by the Oswestry Disability Index (ODI); anxiety and depression symptoms measured by the Hospital Anxiety and Depression Scale (HADS) and the Pain Catastrophizing Scale (PCS); and patient satisfaction measured by the Patient Global Impression of Change Scale (PGIC). Safety will be evaluated by adverse events (AE), serious adverse events (SAE) and device deficiencies from inclusion to 12-month follow-up.

Only for patients enrolled at Poitiers University Hospital: the effects of stimulation modalities on brain imaging will be measured by MRI Blood Oxygen Level-Dependent (BOLD) signal and Fractional Anisotropy (FA) resting state condition (stimulation switch off). Effects of stimulation on brain electrical activity will be measured by EEG signal of the posterior cingulate cortex (PCC), the pregenual anterior cingulate cortex (pgACC) and ventromedial prefrontal cortex (vmPFC), pgACC/vmPFC with stimulation switched on.

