### 2.7. Statistical Analysis

#### 2.7.1. Sample Size and Power Calculations

In the ACCURATE study [24], the authors reported a significant difference between DRGS and conventional SCS for the treatment of the CRPS and causalgia using the following primary end point: “VAS decrease percentage ≥ 50% during lead trial and at 3-month follow-up and no incidence of neurological deficits due to stimulation”. They found that 81.2% of patients (56/69) responded to DRGS vs. 55.7% of patients (39/70) to SCS at 3-month follow-up. These data allowed us to estimate the necessary sample size that suffices to demonstrate a significant difference between the DRGS and conventional SCS. No data are available in the literature concerning DUAL stimulation. We estimate that DUAL stimulation superiority might arise from combining the effects of and mechanisms of action of both stimulation modalities.

With a level of significance at 0.05 and a power of 90%, we found that a number of patients set at 48 should be adequate to demonstrate a significant difference between the success proportions in SCS, DRG and DUAL stimulations in a six-arm crossover design.

Considering the possibility of a potential dropout (17%—lost to follow-up and possible explanted patients, which is the drop-out rate we observed in our previous studies [4,5]), and in order to have a sufficient number of patients allowing us to address secondary objectives, a total of 66 patients are planned to be included in the study.

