Continuous outcomes at 4-month of burst DRGS, burst SCS and burst DUAL stimulations will be compared using an ANOVA or a Kruskal–Wallis test. In case the ANOVA (or Kruskal–Wallis test) is significant, a pairwise comparison will then be conducted using independent *t*-test or Mann–Whitney test depending on the variable distribution. A Holm–Bonferroni correction will be applied on the pairwise comparison.

The categorical outcomes will be compared using a Chi-squared test or an exact Fisher test when the Chi-squared assumptions are not met. A generalized mixed-effects model with a patient specific random intercept will be used to estimate the global treatment effect including the 6-month and 12-month follow-ups. The link function used in the model will depend on the type of the studied outcome (logistic or multinomial for categorical outcomes and no link function for continuous outcome).

The relationship between performance (percentage of pain covered with stimulation) and “induced” pain relief (global pain VAS) will be estimated by Kendall’s tau and its 95% confidence interval. The correlation between selectivity (percentage of paresthesia covering pain) and paresthesia discomfort will also be estimated using Kendall’s tau.

Mean energy consumption will be compared between the different types of stimulation using repeated measures ANOVA or a Friedman test.

Tonic stimulation will be compared to burst stimulation using patient last crossover stimulation modality. The comparison will be conducted using a paired *t*-test or a Wilcoxon signed-rank test using data from the last crossover period compared to the 4-month data using burst stimulation. VAS decrease will be compared between all the SCS modalities at 6-month and 12-month follow-ups using a two-factor ANOVA (preferred anatomical target x preferred stimulation type).

A sub-analysis of the sample will be conducted in order to assess the effect of burst waveform on the brain signals visualized using brain imaging data with and without burst stimulation.

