Two interim analyses are planned. The first interim analysis will be conducted on data from the first 12 patients included (after the “Tonic” crossover period). In this first interim analysis, we will analyze only the safety criteria, the objective being to assess study feasibility. The second interim analysis will be conducted on data from the first 33 patients included (after the “Tonic” crossover period) and will be exclusively descriptive. No hypothesis testing will be conducted. This analysis will be conducted on primary and secondary outcomes. As the study is of long duration (3.5 years), we decided to include a second interim analysis to communicate the results to the scientific community by clearly indicating that this is an interim analysis and that the final analysis will be conducted on the total sample of 66 patients. This may lead to other projects and accelerate the progress of research on the stimulation of several anatomical targets. These results will have no impact on study completion. The final analysis on 66 patients will be considered for the report and the publications.

Only data from the crossover period will be used in the interim analysis. The statistical methods used in this interim analysis will be similar to the methods used in final analysis described above. No adjustment of the final analysis *p*-values will be conducted as the interim analysis results do not influence in any way the course or the conduct of the study.

A significance level of 0.05 will be considered in this study (after taking into account multiple testing corrections) and all tests will be two-sided.

All the analyses will be conducted based on an Intention-To-Treat (ITT) principle using complete cases. No missing data imputation will be conducted. An initial safety analysis will be conducted on the first 12 patients to assess the initial safety of implementing patients with both DRG and SCS stimulations. A final safety analysis will be conducted on the 66 patients. Frequencies of adverse events and deviations from protocol will be compared between the treatments following an ITT analysis.

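### The month-4 burst comparison is a randomised between-patient comparison of about 18 to 22 patients per modality, analysed without baseline as a covariate; this is valid but less precise than ANCOVA

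*Protocol article*

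**What the plan says.** **Allocation.** Section 2.1: "Patients will be randomized in 6 different arms in a 1:1:1:1:1:1 ratio". There are three modalities and six arms. After the third period, section 2.6 has all patients switch to burst for one month "while keeping the last allocated stimulation type in the randomized crossover arm". Each patient therefore contributes month-4 burst data on one modality only. From month 4 on, patients choose their own modality and waveform (section 2.1).

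**Analysis.** Section 2.7.2: "Continuous outcomes at 4-month of burst DRGS, burst SCS and burst DUAL stimulations will be compared using an ANOVA or a Kruskal–Wallis test". If that test is significant, pairs are compared by independent t-test or "Mann–Whitney test depending on the variable distribution", with a Holm–Bonferroni correction. No covariate is named. The same section adds: "All the analyses will be conducted based on an Intention-To-Treat (ITT) principle using complete cases".

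**Outcome definition.** Section 2.5.2 says that the secondary outcomes compared between treatments and waveforms "are changed between baseline and each follow-up visit". Section 2.7.2 does not say whether the month-4 comparison uses these changes or the raw month-4 values.

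**Baseline data.** Table 1 places VAS, ODI, HADS, PCS, EQ-5D-5L and mapping of the painful territory at the inclusion visit. Section 2.5.1 takes the pain-diary baseline before lead implantation.

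**Size.** Section 2.7.1: "a total of 66 patients are planned to be included in the study", with 17% dropout allowed for. Power is stated only for the primary crossover comparison.

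**The concern.** In months 1 to 3 each patient serves as his or her own control. That advantage is gone at month 4, where three modest independent groups are compared and between-patient variation falls fully into the error term. Part of that variation can be predicted from the pre-implantation score, which is already collected. ANOVA, Kruskal–Wallis, t and Mann–Whitney tests as named do not make use of it as a covariate. Subtracting it, as section 2.5.2 implies, fixes its coefficient at 1, which is seldom the best value.

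At stake is the precision of the only randomised comparison of the three targets under burst, since modality and waveform are self-selected afterwards. Adjustment would also remove chance baseline differences between the groups from the estimates.

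**Working it through.** **Plan's own figures.** Section 2.7.1 gives 48 patients for the primary comparison. Allowing for 17% loss, 48/0.83 = 57.8, so 58, and the planned 66 covers this. The 48 itself can be neither confirmed nor faulted, because the DUAL response rate and the within-patient correlation are not given. No power or precision is stated for month 4, so there is no figure to reproduce there.

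**Group size.** With six orderings of three modalities in equal ratio, one third of patients end on each modality.
- No loss: 66/3 = 22.
- After 17% loss: 66 × 0.83 = 54.8, and 54.8/3 = 18.3.
- If only the required 48 remain: 48/3 = 16.

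**What these groups can detect.** For an unadjusted two-sided t-test with 80% power, in SDs of the variable analysed:
- n = 18: 0.96 SD at 0.05; 1.13 SD at the first Holm step (0.05/3 = 0.0167).
- n = 22: 0.87 SD at 0.05; 1.01 SD at 0.0167.

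**Variance per patient.** Set the SD to 1 at both baseline and month 4 (assumption), with correlation r (assumption):
- raw month-4 score: 1
- change score: 2(1 - r)
- ANCOVA: 1 - r²

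ANCOVA relative to raw is then 1 - r². Relative to change it is (1 - r²)/[2(1 - r)] = (1 + r)/2.

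| assumed r | ANCOVA / raw | ANCOVA / change |
|---|---|---|
| 0.2 | 0.96 | 0.60 |
| 0.3 | 0.91 | 0.65 |
| 0.5 | 0.75 | 0.75 |
| 0.7 | 0.51 | 0.85 |

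At r = 0.5, 18 patients per group give the precision of 18/0.75 = 24. The detectable difference falls from 0.96 to 0.83 raw SD at n = 18, and from 0.87 to 0.75 at n = 22.

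**Power for one pair.** Assumed difference 0.8 raw SD, two-sided 0.05, noncentral t, ignoring the one degree of freedom that ANCOVA uses (raw / change / ANCOVA):

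| assumed r | n = 18 | n = 22 |
|---|---|---|
| 0.2 | 65 / 45 / 66% | 74 / 54 / 75% |
| 0.3 | 65 / 50 / 69% | 74 / 59 / 78% |
| 0.5 | 65 / 65 / 77% | 74 / 74 / 85% |
| 0.7 | 65 / 85 / 90% | 74 / 92 / 95% |

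**If the variances differ.** Let the month-4 SD be k times the baseline SD. The change-score variance is 1 + k² - 2kr and the ANCOVA variance is k²(1 - r²). Their difference is 1 - 2kr + k²r² = (1 - kr)², which is never negative. The direction therefore does not need equal variances. The size does, and the gain over change scores vanishes as kr approaches 1.

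**Which outcomes have a baseline.** In Table 1, paresthesia discomfort starts at M1, paresthesia mapping (hence coverage and selectivity) exists only after implantation, and so does PGIC. None has a pre-stimulation value to adjust for.

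**The case against.** The strongest reply is that nothing here is wrong. The final modality is randomised, so an unadjusted comparison of raw or change scores is valid and unbiased over randomisation. The comparison is secondary, no power is claimed for it, and covariates are often left to an analysis plan. This stands as to validity and importance. It does not remove the point, because the article names the tests itself and a more precise analysis is available from data already collected.

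Several stronger readings are tempting and are not supported:
- *Baseline is ignored.* Section 2.5.2 defines the outcomes as changes from baseline. The supportable statement is that baseline is not used as a covariate.
- *These are the smallest groups in the trial.* Section 2.7.2 also plans a two-factor ANOVA at 6 and 12 months, of preferred target by preferred stimulation type. That has up to six cells, averaging 66/6 = 11 patients before loss.
- *The article's first-in-humans claim rests on this test.* The Introduction and Discussion attach that claim to burst applied to the DRG. The paired tonic-versus-burst comparison also bears on it.
- *The gain is known to be large.* It depends on r, which the article does not give. Against raw scores at r = 0.2 it is only 4% of the variance. For VAS, the entry threshold of 5/10 and the required 50% relief in the trial phase could lower r and make the two variances unequal.

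It is also fair to object that adjustment cannot be applied to every outcome. Responder outcomes, for instance, are already defined relative to baseline and have no baseline value of their own.

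**Conclusion.** The point holds as a matter of efficiency. The month-4 burst comparison is between independent randomised groups of about 18 to 22, and the named tests do not use baseline as a covariate. Whether the raw or the change score is analysed, ANCOVA is at least as precise, apart from one degree of freedom. Over assumed r from 0.2 to 0.7 and with equal variances, it reduces residual variance by 4% to 49% against raw scores and by 40% to 15% against change scores. The direction is firm; the size rests on those two assumptions. A reader might infer that the planned tests are biased or that the main result is weakened. Neither follows: the tests are valid, and the primary crossover analysis is unaffected.

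**What to change.** For continuous outcomes with a pre-implantation value (VAS, ODI, HADS, PCS, EQ-5D-5L, pain surface), replace the month-4 ANOVA and t-tests with a linear model: month-4 score on final modality (three levels) plus the pre-implantation value of the same outcome. Take the pairwise contrasts from that model, Holm-adjusted. If residuals are clearly non-normal, use a rank-based ANCOVA or robust standard errors; this replaces the Kruskal–Wallis and Mann–Whitney route for these outcomes.

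Do not adjust for the month-3 value: it is measured after randomisation on the same modality and already carries the treatment effect.

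Keep the planned tests for PGIC, paresthesia discomfort, and paresthesia coverage and selectivity, which have no pre-stimulation value, and for responder outcomes.

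Suggested wording: *Month-4 continuous outcomes with a pre-implantation measurement will be compared by ANCOVA with final modality as factor and the pre-implantation value as covariate; pairwise contrasts will be Holm-adjusted.*

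The cost is this wording, the list of outcomes to which it applies, and one degree of freedom per model. No extra data or patients are needed.
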